## Abstract

**Background:**

Kidney failure requiring dialysis is associated with poor health outcomes and health-related quality of life (HRQL). Patient-reported outcome measures (PROMs) capture symptom burden, level of functioning and other outcomes from a patient perspective, and can support clinicians to monitor disease progression, address symptoms, and facilitate patient-centered care. While evidence suggests the use of PROMs in clinical practice can lead to improved patient experience in some settings, the impact on patients’ health outcomes and experiences is not fully understood, and their cost-effectiveness in clinical settings is unknown. This study aims to fill these gaps by evaluating the effectiveness and cost-effectiveness of routinely measuring PROMs on patient-reported experience, clinical outcomes, HRQL, and healthcare utilization.

**Methods:**

The EMPATHY trial is a pragmatic multi-centre cluster randomized controlled trial that will implement and evaluate the use of disease-specific and generic PROMs in three kidney care programs in Canada. In-centre hemodialysis units will be randomized into four groups, whereby patients: 1) complete a disease-specific PROM; 2) complete a generic PROM; 3) complete both types of PROMs; 4) receive usual care and do not complete any PROMs. While clinical care pathways are available to all hemodialysis units in the study, for the three active intervention groups, the results of the PROMs will be linked to treatment aids for clinicians and patients. The primary outcome of this study is patient-provider communication, assessed by the Communication Assessment Tool (CAT). Secondary outcomes include patient management and symptoms, use of healthcare services, and the costs of implementing this intervention will also be estimated. The present protocol fulfilled the Standard Protocol Items: Recommendations for Intervention Trials (SPIRIT) checklist.

**Discussion:**

While using PROMs in clinical practice is supported by theory and rationale, and may engage patients and enhance their role in decisions regarding their care and outcomes, the best approach of their use is still uncertain. It is important to rigorously evaluate such interventions and investments to ensure they provide value for patients and health systems.

**Trial registration:**

Protocol version (1.0) and trial registration data are available on www.clinicaltrials.gov, identifier: NCT03535922, registered May 24, 2018.

## Background

At the end of 2018 there were over 40,000 Canadians with kidney failure requiring dialysis; a 35% increase from the previous decade [1]. Kidney failure requiring dialysis is associated with high symptom burden and poor health-related quality of life (HRQL) [2] [3] [4] [5]. Patients can experience a wide variety of symptoms ranging from physical to psychological in nature [6]. These symptoms are often under-recognized by kidney care teams, which may be related to breakdown in communication [7]. In a recent priority setting exercise, the top research priority for patients with kidney failure requiring dialysis in Canada was to enhance communication between patients and clinicians to maximize patient participation in decision making and facilitate self-management [8]. Furthermore, five of the top 10 research priorities for patients with kidney failure requiring dialysis focus on reducing symptoms and improving HRQL [6].

The priorities of enhancing communication and improving symptoms and HRQL are potentially well aligned. In other chronic diseases, the incorporation of routinely measuring and reporting symptoms and HRQL improved communication [9–11]. Without routine symptom monitoring, this situation is unlikely to change. Further, the presence and severity of symptoms can change considerably over a short period of time in dialysis patients, emphasizing the need for regular surveillance of symptoms. Incorporation of patient-reported outcome measures (PROMs) into dialysis care could address this problem.

### What are PROMs?

PROMs are reports coming directly from patients about how they function or feel in relation to a health condition and its therapy, without interpretation of the patient’s responses by a clinician or anyone else [12]. PROMs present an opportunity to explore aspects of patients’ health that may otherwise be overlooked. They capture patients’ experiences of symptoms and impact of disease on functioning and can support clinicians to monitor disease progression and facilitate patient-centered care. It is proposed that PROMs could act to improve the quality of care in the same way as any other benchmarking tool [13], and some suggest that PROMs have the potential to transform healthcare [14]. There has been an increased use of PROMs in health systems around the world, a movement initiated and led by the National Health System (NHS) in the UK [13]. In Canada, the Canadian Institute for Health Information (CIHI) and the Alberta PROMs and EQ-5D Research and Support Unit [15] are leading similar efforts to establish provincial and national PROMs strategies and support the use of PROMs in the Canadian healthcare system [15, 16].

### PROMs in clinical practice

Although PROMs have become widely used in clinical effectiveness research, their usefulness in clinical settings is still unclear. In the clinical context, ideally PROMs results would be fed back to clinicians who would use that information to improve patient care, much like routine clinical laboratory measures [17]. However, since PROMs were generally not developed or applied for this purpose, little is known about how they perform in this context. A limited number of randomized controlled trials have examined the impact of using PROMs in clinical practice, particularly in oncology, and found that the routine measurement of PROMs, followed by reporting of results to clinicians and patients, had a positive impact on patient-provider communication, patient satisfaction with care, and HRQL [9, 18–24]. Similarly, in adolescents with type 1 diabetes, the periodic monitoring and discussion of PROMs led to improvement in psychosocial wellbeing, however, this benefit was not sustained after the completion of the intervention [25, 26]. In patients with gastrointestinal disorders, the one-time use of a disease-specific PROM had no impact on patient satisfaction, provider interpersonal skills, or shared decision-making [24].

Systematic reviews of these clinical trials and others suggest that feedback of PROMs to clinicians have an impact on processes of care, may enhance patient-provider relationship, improve communication, and support shared decision-making [27–30]; however, their impact on health outcomes is less apparent [27, 31–33]. Aside from these limited controlled studies examining the clinical effectiveness of PROMs themselves as an intervention, few studies have examined their value and cost-effectiveness to justify their use in clinical practice [34].

Additionally, qualitative studies that explored practical issues surrounding the implementation of PROMs in clinical practice found that demonstrating clinical utility to clinicians is a key factor for successful and effective implementation of PROMs [35, 36]. Other factors identified include the use of technology, having the appropriate infrastructure in place, embedding PROMs into routine workflow, improving the interpretability of PROMs data, and engaging clinicians in the planning phase of the intervention [35]. Finally, a key element identified by clinicians is the linkage of PROMs with tools to support the clinical management of symptoms or problems identified by assessments [37]. For example, if a patient identifies problems with anxiety or depression, clinicians should have readily available treatment protocols to follow to alleviate those symptoms [35, 36]. Although the current evidence on the impact of PROMs on patient outcomes is relatively limited and has several methodological limitations, it generally suggests that the effectiveness of PROMs depends on the function of the PROM and the type of feedback provided.

PROMs can be generic or disease-specific, and each has several advantages and disadvantages [38]. Generic measures are used to compare outcomes across different populations and interventions, particularly for cost-effectiveness studies and health system decision-makers. Disease-specific measures assess the health status of a specific patient population and may be more sensitive for the detection and quantification of changes that are important to clinicians or patients. A common recommendation in clinical research with PROMs is to combine both a generic and a disease-specific measure for use in a particular patient population, especially when PROMs are used to monitor health and how it changes over time. The presumed benefit of this combination is to broaden the scope of measurement and allow for different uses of the measures (e.g., comparison within versus across disease populations). However, evidence to support this recommendation is limited. In fact, in a study examining the usefulness of generic and disease-specific measures of health status in patients with Alzheimer’s, the EQ-5D (a generic measure) was found to be a suitable alternative to a disease-specific measure of health [39]. Another study reported that generic and disease-specific measures performed similarly in assessing changes in HRQL in patients with kidney failure requiring hemodialysis [40]. There is usually some level of overlap between generic and disease-specific measures, and the need for combining both types of measures depends on the target patient population and the constructs assessed by each measure. Given the workload associated with collecting and using PROM data in clinical settings, it is imperative to explore whether one single PROM is sufficient to improve patient-provider communication, processes of care, and ultimately patient outcomes, before recommending the use of a combination of generic and disease-specific measures.

### Justification for PROMs in dialysis care

One of the key areas where PROMs have been implemented is in patients with kidney failure requiring dialysis. The prevalence of chronic kidney disease (CKD) is relatively high in Canada (12.5% or 3 million Canadian adults) and its advanced stages can lead to kidney failure [41]. Kidney failure requiring dialysis is expensive and is associated with poor health outcomes and HRQL. To report symptom burden and HRQL alongside clinical and laboratory measures, it is imperative to measure and report what is important to patients. PROMs could be used to evaluate and monitor patients’ health, inform care planning, and facilitate the introduction of treatments for patients with kidney failure requiring dialysis [42].

Moreover, the implementation of PROMs assessments and integration into the workflow of a busy clinical setting such as dialysis clinics requires a feasible system to capture and report PROMs. This would be facilitated by the development of PROM report cards to present results to clinicians and patients in a manner that is easily understood and interpretable, analogous to clinical laboratory measures used in the hemodialysis setting. We believe that routine hemodialysis care provides the ideal setting for implementation and rigorous evaluation of a PROM intervention, and as such, we are conducting a pragmatic, cluster randomized controlled trial (RCT) of a PROMs intervention. Our comprehensive evaluation will assess the effectiveness of this intervention, the adoption and implementation in the busy clinical setting of hemodialysis units, as well as the cost-effectiveness of PROMs in routine hemodialysis care.

## Aims of the research

The overall aim of this study is to explore the usefulness of integrating PROM assessments in the clinical management of hemodialysis patients. Specifically, the primary objective is to determine the effects of routine measurement and reporting to clinicians of PROMs, namely, the Edmonton Symptom Assessment System- revised: Renal (ESAS-r: Renal) [43] [44], or the Integrated Palliative care Outcome Scale – Renal (IPOS-Renal) [45] and/or the EQ-5D-5L [46] on patient-reported experience, particularly patient-clinician communication, measured by the Communication Assessment Tool (CAT), for patients with kidney failure requiring hemodialysis. The secondary objectives are as follows:
i.To determine if there is a difference in patient-reported experience and other outcomes induced by a condition specific (ESAS-r: Renal /IPOS-Renal) versus a generic (EQ-5D-5L) PROM;ii.To determine the effects of routinely measuring and reporting the ESAS-r: Renal/IPOS-Renal and/or the EQ-5D-5L on the clinical management of symptoms;iii.To determine the effects of routinely measuring and reporting the ESAS-r: Renal /IPOS-Renal and/or the EQ-5D-5L on overall HRQL;iv.To determine the effects of routinely measuring and reporting the ESAS-r: Renal/IPOS-Renal and/or the EQ-5D-5L on symptom burden, mental health outcomes and healthcare utilization;v.To determine the cost effectiveness of routinely measuring the ESAS-r: Renal/IPOS-Renal and/or the EQ-5D-5L for patients with kidney failure requiring hemodialysis;vi.To explore the perspectives and experience of patients and clinicians with routine measurement and reporting of PROMs in clinical practice.

## Methods

### Study design

To date, the effect of PROMs on patient outcomes were generally assessed in conventional parallel-group RCTs of individuals. Few convincingly demonstrated benefits to patient-important outcomes, which might be in part due to contamination effects and small sample sizes [47]. This study uses a cluster RCT design, with clustering occurring at the level of individual hemodialysis units, to reduce potential contamination between the study groups (Fig. 1). EMPATHY is an open-label RCT, since blinding is not feasible [48]. Consequently, research staff, clinicians, and all patients are aware of group allocation. Dialysis units, stratified by three regions (Northern Alberta, Southern Alberta, and Ontario), were randomly allocated using random number sequences with all units from a region randomized on the same day. Dialysis units were allocated in a 1:1:1:1 ratio into four groups:
Group 1: Patients complete ESAS-r: Renal or IPOS-RenalGroup 2: Patients complete EQ-5D-5LGroup 3: Patients complete both ESAS-r: Renal or IPOS-Renal and EQ-5D-5LGroup 4: Usual care (i.e. the control group). To assess study outcomes, patients complete the PROMs at baseline, 6 and 12 months, but these data are not reported back to clinicians or patients.

**Fig. 1 Fig1:**
[figure not shown]
**Schematic of overall design for the EMPATHY Study.** *Outcome measures survey includes: Communication Assessment Tool (CAT), Patient Assessment of Chronic Illness Care 11-items questionnaire (PACIC-11), Patient Health Questionnaire 2-item (PHQ-2), General Anxiety Disorder 2-items questionnaire (GAD-2), Edmonton Symptom Assessment System – revised: Renal (ESAS-r: Renal) or Integrated Palliative care Outcome Scale – Renal (IPOS-Renal), and/or EQ-5D-5L

### Interventions

Groups 1–3 will collect their allocated PROM(s) from all eligible patients every 2 months, for 12 months (a total of 7 assessments). PROMs are administered by pen and paper or through an electronic platform on a tablet in accordance with hemodialysis unit resources. In Alberta, the electronic medical records (EMRs) generate a PROM report card with a symbol scheme for nurses to follow up with clinical management where applicable. The symbol scheme comprises of a check mark for no problems/symptoms (ESAS-r: Renal = 0, IPOS-Renal = 0, EQ-5D-5L = 1) a caution sign for mild problems/symptoms (ESAS-r: Renal = 1–3, IPOS-Renal = 1, EQ-5D-5L = 2) and a stop sign for moderate-severe symptoms/problems (ESAS-r: Renal = 4–10, IPOS-Renal = 2–4, EQ-5D-5L = 3–5). The PROM report card is printed and added to the patient’s medical chart for review by clinicians (i.e., nurses, nephrologists, and allied health professionals). The report displays each patient’s most recent PROM scores in comparison with their previous scores, much like lab test results. A sample PROM report card is shown in Fig. 2. In Ontario, EMRs do not have report card capabilities and units store the paper-completed PROM questionnaires in the patient’s medical chart, along with previously completed questionnaires for review by clinicians and the patient. In all locations, PROMs are accompanied by treatment aids for some symptoms assessed (pain, pruritus, restless legs, sleeping problems, tiredness, nausea, shortness of breath, anxiety, and depression). Patients are also offered a copy of their PROM report card (if possible) and patient-facing self-management guides for symptom management. This trial is intended to generate evidence on the implementation within the health systems. While we will aim to maintain the study design and key elements of the intervention as consistently as possible, we will allow for the interventions to be tailored to local health systems, accommodating considerations such as the clinical work flow, information systems and capabilities, and internet/WiFi access (Table 1).

**Fig. 2 Fig2:**
[figure not shown]
Sample EQ-5D-5 L PROMs Report Card

**Table 1 Tab1:** Intervention similarities and differences between renal programs

**Setting**	•All three renal programs will implement the intervention in in-centre hemodialysis units only, excluding home hemodialysis and peritoneal dialysis units •The three geographically based renal programs have similar models of multi-disciplinary care
**Disease-specific PROM Use**	•AKC-N and ORN will use the ESAS-r: Renal •ACK-S will use the IPOS-Renal
**Generic PROM Use**	All renal programs will use the EQ-5D-5 L
**Frequency of PROMs**	All renal programs will administer the PROM(s) every 2 months
**Mode of PROMs Administration**	•ORN: clinicians will administer PROMs by paper and store in patients’ charts •AKC-N: clinicians will administer PROMs by paper and then enter PROMs results into their EMR •AKC-S: clinicians will administer PROMs by iPad, directly entering results into their EMR
**PROMs Report Cards**	•AKC-N and AKC-S will generate a PROMs report card with a symbol scheme categorizing symptoms/problems into ‘no symptom/problem present’, ‘mild symptom/problem’ and ‘moderate-severe symptom/problem’ •ORN will simply use the completed PROM(s) for review and discussion
**Treatment Aids**	Each renal program developed their own symptom guidelines for clinicians and patient information handouts
**Clinical Workflow**	All renal programs will deliver the EMPATHY intervention in 3 phases: 1. Screening: PROM(s) are administered every 2 months 2. Assessment: Clinician reviews PROM(s) results with the patient and discuss where management is needed 3. Management: Clinician uses the treatment aids to manage symptoms, as applicable
**Outcome Measures Survey Frequency**	All renal programs will collect the outcome measures through a survey collected at baseline, 6 months, and 12 months
**Outcome Measures Survey Mode of Administration**	•AKC-N and AKC-S will administer the outcome measures survey by iPad, with a paper back-up (e.g., where wifi access not available) •ORN will administer the outcome measures survey by paper
**Clinician Training**	•Each renal program will deliver their own training of the intervention to clinicians as the intervention is slightly different across the renal programs •The overall delivery of education between the three programs will be very similar, using a ‘train-the-trainer’ approach, whereby clinical leaders will first be trained at each site and these leaders will then train relevant clinicians using their usual mechanisms of disseminating new clinical information/policy and procedures •Within each renal program, each unit will name a staff member to act as the ‘EMPATHY site lead’ to champion the trial in the unit and act as a liaison between the unit and the research team

### Hypotheses

We hypothesize that the measurement and reporting of the ESAS-r: Renal or IPOS-Renal, EQ-5D-5L or a combination every 2 months will lead to improved patient-clinician communication in dialysis units. We also hypothesize that this will lead to reduced symptoms and improved mental health and HRQL. Furthermore, we anticipate that this intervention will be cost-effective and will be acceptable and feasible in the hemodialysis units’ environment.

### Setting and population

Dialysis programs frequently provide administrative functions for separate hemodialysis units; however, the unit of randomization is the dialysis unit, not dialysis programs or individual patients. In total, 44 units from three renal programs were randomly allocated to one of the four study groups. We enrolled all eligible hemodialysis units in Alberta, including 17 hemodialysis units from the Alberta Kidney Care - North (AKC-N) program and 12 units from the Alberta Kidney Care - South (AKC-S) program. Of Ontario’s 92 hemodialysis units, 15 enrolled in the study, based on voluntary acceptance of invitation to participate.

### Dialysis unit eligibility criteria

Hemodialysis units meeting the following inclusion criteria were included in this study:
The unit provides chronic in-center hemodialysis;Hemodialysis clinicians are willing to review individual patients’ routinely collected ESAS-r: Renal or IPOS-Renal and/or EQ-5D-5L as part of routine patient assessment;

Hemodialysis units are excluded if they meet any of the following criteria:
The unit is unable to administer the ESAS-r: Renal or IPOS-Renal and EQ-5D-5L to in-centre hemodialysis patients as part of clinical workflow to all possible patients;The unit is part of a long-term care facilityThere are 5 or fewer patients treated at that unitLack of WiFi connectivity (Alberta only)

### Patient eligibility criteria

All patients undergoing chronic hemodialysis who are 18 years or older at the start of the study and are willing and able to complete the PROMs as part of the trial are eligible to participate in this study. Patients with cognitive impairment, undergoing acute dialysis, or transiently dialyzing in the unit are not included. Simplified Chinese, Punjabi, and Vietnamese PROMs and study surveys were provided. Patients that had other language barriers had family help them complete their PROMs assessments and/or study surveys or the health system interpretive services were used. For patients with eyesight issues, their family members or nurses helped them complete the PROMs and study surveys.

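### Patient eligibility is tied to willingness to complete the PROMs, a commitment that differs by arm, so the criterion permits (but is not shown to cause) different patient selection in Groups 1–3 and Group 4

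*Protocol article*

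**What the plan says.** Under Patient eligibility criteria, the article limits participation to adults on chronic hemodialysis who are "willing and able to complete the PROMs as part of the trial are eligible to participate in this study". The sentence does not say which PROMs or which schedule it means.

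The schedule depends on the arm:

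- **Groups 1–3** (Interventions): "Groups 1–3 will collect their allocated PROM(s) from all eligible patients every 2 months, for 12 months (a total of 7 assessments". Nurses administer the PROMs (Clinician training). In the workflow row of Table 1, "Clinician reviews PROM(s) results with the patient and discuss where management is needed".
- **Group 4** (Study design): "To assess study outcomes, patients complete the PROMs at baseline, 6 and 12 months, but these data are not reported back to clinicians or patients". The Methods paragraph of the abstract instead says that control patients "receive usual care and do not complete any PROMs".

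The unit of randomisation is the dialysis unit. Under Study design, "research staff, clinicians, and all patients are aware of group allocation". The outcome survey, which carries the CAT, is scheduled at baseline, 6 and 12 months in all three renal programs (Table 1). Utilization comes from provincial administrative databases.

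**The concern.** A patient-level entry criterion in an open cluster trial should mean the same thing in every arm. Here it refers to the intervention itself. A patient who would answer three study surveys but does not want a questionnaire every two months, discussed with staff, can fail the criterion in an intervention unit and meet it in a control unit.

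The primary analysis compares Groups 1–3 pooled with Group 4, which is the line along which the commitment changes. If patients who decline PROMs differ in how they rate communication, in symptoms or in use of care, the comparison would mix the effect of PROMs with a difference in who was counted. The criterion is also unnecessary for these outcomes. A patient who declines routine PROMs can still answer the CAT, and administrative utilization data need no PROM.

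**Working it through.** **1. Count of rounds.** The stated seven is reproduced: 12/2 + 1 = 7 (months 0, 2, 4, 6, 8, 10, 12). Group 4 has 3 (months 0, 6, 12).

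| | Groups 1–3 | Group 4 |
|---|---|---|
| Intervention PROM rounds | 7 | none |
| Outcome surveys | 3 | 3 |
| Results reviewed with the patient | yes | no |

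**2. What the criterion refers to.** Later in the same paragraph, PROMs and study surveys are listed as separate items. The natural reading of the criterion is therefore the PROM assessments and not the survey. The Interventions section then collects the allocated PROMs from all eligible patients, which ties eligibility to the intervention.

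**3. Timing.** All units in a region were randomised on the same day (Study design), but AKC-S and ORN brought units in at different points (Study timelines). The analysis section also notes patients entering and leaving units. Willingness can therefore be judged with allocation known.

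**4. Size.** Let f be the extra fraction of patients not counted in intervention units, and d the CAT gap between those counted and those not. The mean over everyone is (1 − f) × mean(in) + f × mean(out) = mean(in) − f × d. The counted mean is therefore shifted by f × d. The documents give neither f nor d, so both are assumed. The SD of 0.74 and the detectable effect of 0.23 come from Sample size and power. I use 0.23 only as a yardstick. The article does not state its unit, so both readings are shown.

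| f (assumed) | d (assumed) | f × d, CAT points | Share of 0.23 points | Share of 0.23 SD |
|---|---|---|---|---|
| 0.05 | 0.25 SD = 0.185 | 0.009 | 4% | 5% |
| 0.10 | 0.5 SD = 0.37 | 0.037 | 16% | 22% |
| 0.20 | 0.5 SD = 0.37 | 0.074 | 32% | 43% |
| 0.30 | 1.0 SD = 0.74 | 0.222 | 97% | 130% |

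**5. Baseline adjustment.** The primary model adjusts for the unit's baseline mean CAT. If selection shifts the intervention units by b0 at baseline and b12 at 12 months, and the covariate has slope β, the bias left in the adjusted contrast is b12 − β × b0. Selection already present at baseline is partly offset. Selection that develops afterwards (b0 = 0) is not offset at all. Because the CAT surveys are anonymous, individual responders cannot be followed between visits to see which has happened.

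**The case against.** The strongest reply is that the article states one criterion for all arms and never says that it means seven rounds in one and three in another. PROMs are also part of the outcome survey (Fig. 1 legend), and Study design uses the same language for outcome collection in Group 4. On that reading, the condition is simply willingness to answer the trial's questionnaires. The survey runs on the same three visits in every program, Groups 1–3 receive it too, and no passage restricts it to patients who accept the two-monthly rounds. Since CAT forms are anonymous, a response cannot be removed at analysis because its author refused PROMs. Selection on the CAT would have to occur when the survey is offered.

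Most of this stands as a limit on the claim. A reader might infer that the outcome-supplying patients are in fact selected differently, that this favours PROMs, or that the bias is as large as the effect sought. The documents support none of these:

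- They give no refusal or response rates by arm.
- Direction is open. Patients with few symptoms might decline as readily as those on poor terms with staff.
- The upper figure multiplies the two most extreme assumed inputs and ignores baseline adjustment.

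Nor is the control task simply lighter. Each survey includes the CAT, PACIC-11, PHQ-2, GAD-2 and PROMs, whereas a Group 2 round is five items plus a visual analogue scale. What differs is frequency and clinician review.

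The reply does not remove the point. The criterion is a rule that the article states, so this is not a detail left to a fuller document. At best its wording is ambiguous, and an ambiguous criterion applied with allocation known still allows arm-dependent selection.

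**Conclusion.** The point holds as a risk that the stated criterion creates. Eligibility is not defined independently of arm, and as written it permits different selection in Groups 1–3 and Group 4. The CAT and other survey outcomes could be affected. Utilization could be too, although the article does not say how decliners are handled there.

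The illustrative range is about 0.01 to 0.22 CAT points before baseline adjustment, with 0.074 for f = 0.20 and d = 0.5 SD. It rests entirely on assumed f and d. It shows that moderate differential refusal would matter beside 0.23, not that it took place. The wording should be corrected because that is inexpensive; the finding does not invalidate the trial.

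**What to change.** 1. Define the outcome population identically in all four groups: adult chronic in-centre hemodialysis patients who meet the other criteria.
2. Offer all of them the survey at 0, 6 and 12 months, whether or not they accept the two-monthly PROMs. A self-reported outcome still needs a willing and able respondent, so keep that condition for the survey alone.
3. Include all of them in the utilization analysis where linkage permits.
4. Treat refusal of PROMs as non-adherence within the assigned group.
5. Report eligible and responding numbers by unit and visit.
6. Reconcile the abstract with Study design on whether control patients complete PROMs.

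The cost is a wording amendment, an instruction to sites and the counts. By the article's timelines, AKC-N (17 of 44 units) completed its trial year in October 2019, so only the analysis population and the reporting can change there. An instruction on offering the survey can help only where AKC-S and ORN units are still collecting data. The downside is that patients who never used the PROMs remain in Groups 1–3, so the estimated effect may be slightly diluted.
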